#### Missing data

First, all analyses will be performed without taking into account missing values. Second, a sensitivity analysis will be performed using multiple imputations to replace missing values where appropriate for primary and all secondary outcomes [34]. We will create 10 copies of the dataset, with the missing values replaced by imputed values, based on observed data including outcomes and baseline characteristics of participants. Each dataset will be analyzed using standard statistical methods, and the results from each dataset will be pooled into a final result using Rubin’s rule.

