### Definitions

“Non-invasive ventilation” refers to a bilevel positive pressure ventilation applied via a non-invasive interface (a face mask); “music intervention” refers to a receptive music session administered to a patient by trained caregivers; “respiratory comfort” refers to a “0” rate on a 10-cm dyspnea visual analog scale; “NIV intolerance” refers to the need for the premature cessation of an NIV session; “NIV failure” is defined by the need of endotracheal intubation.

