#### “Musical intervention" group

NIV is conducted as detailed above, including visual isolation. The musical intervention is initiated starting from the first NIV session that follows randomization.Once the NIV mask has been fitted and the ventilator settings optimized, the trained nurse or nursing assistant sets up the headphones (BOSE AE2®), presents the tablet interface (Samsung Galaxy®), and shows the patient how to handle it.The patient’s musical tastes are determined by a caregiver-administered questionnaire, either to the patient or to her relatives if the patient is unable to express her musical choices (moderate impairment of consciousness). The patient therefore chooses the musical program, with MUSIC CARE^©^ software [19, 24, 25], according to her musical preferences, sets the volume level, and runs the musical session.The musical intervention session lasts 30 minutes and contains two phases, called an L-type sequence (Fig. 2) [24]; the downswing phase is achieved by reducing the musical rhythms starting at high tempos and a high number of instruments, gradually leading to slower tempos and reducing the number of instruments, the frequencies, and the volume. Then the patient is moved through a maximum relaxation phase with a slow-paced rhythm and reduced orchestras, resulting in maximum relaxation (bottom of the “L”).If the patient asks for more than 30 minutes of musical intervention, the session is extended towards a ”U-type” [25].

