## Study endpoints

### Primary endpoint

The primary endpoint is the change in respiratory comfort before the initiation and after 30 minutes of the first NIV session after randomization. The respiratory comfort will be measured using a digital visual scale [14]. This scale is a 10-cm long ruler, shaped like an arrow. It is bounded on the left by “0: no respiratory discomfort” (the smaller base of the arrow) and on the right by “10: maximal respiratory discomfort” (the larger base of the arrow).

The participant marks the level of his/her perception of discomfort directly on the ruler.

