#### Primary endpoint

The change in respiratory comfort at initiation and after 30 minutes of the first NIV session will be analyzed in the intention-to-treat population. For each patient, the variation in respiratory comfort will be calculated by the difference between the measurement at “30 minutes” and "before." This change will then be compared between the treatment groups, based on a Student’s *t* test. If the test application conditions are not met, a Wilcoxon test will be applied.

Because three parallel groups are included in the study, three comparisons are possible: "musical intervention" and "NIV only" (comparison 1), "sensory deprivation" and "NIV only" (comparison 2), and "musical intervention" and "sensory deprivation" (comparison 3). These comparisons will be performed in a pre-established hierarchical test procedure (see Fig. 3), in order to maintain the alpha risk of 5 % in a strong sense:Step 1: We will perform comparisons 1 and 2, both at 2.5 % (bilateral) alpha risk.Step 2: In the event of non-significance of the two previous tests, we will stop the test procedure and conclude the negativity of the trial; in the case of statistical significance of both previous tests, we will perform comparison 3 at 5 % (bilateral) alpha risk; in the case of statistical significance of only one of the two previous tests, we will perform comparison 3 at 2.5 % (bilateral) alpha risk.Step 3: If comparison 3 was performed at 2.5 % alpha risk and is significant, the non-significant comparison performed in step 1 may be performed again at an alpha risk of 5 % (Fig. 3).

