#### Other analyses

All secondary analyses will be performed in the intention-to-treat population (all randomized patients) and also in the per protocol population (patients with no major deviation of the protocol) at a bilateral 5 % alpha risk.

Unless otherwise specified, categorical variables will be compared by a chi-squared test or Fisher test as appropriate. Continuous variables will be compared by a Student's *t* test or Wilcoxon test as appropriate (when two groups are compared) and by an analysis of variance (ANOVA) or Kruskal-Wallis test as appropriate (when more than two groups are compared).

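### The primary analysis is labelled intention-to-treat but is complete-case, and no rule says how a first NIV session that ends before 30 minutes enters the endpoint

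*Protocol article*

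**What the plan says.** The Study endpoints section defines the outcome: "The primary endpoint is the change in respiratory comfort before the initiation and after 30 minutes of the first NIV session after randomization". It is a self-report: "The participant marks the level of his/her perception of discomfort directly on the ruler". The Statistical analysis section (Primary endpoint) says that for each patient "the variation in respiratory comfort will be calculated by the difference between the measurement at" 30 minutes and the measurement before the session, so both values are needed. It adds that this change "will be analyzed in the intention-to-treat population". Other analyses spells that population out: "intention-to-treat population (all randomized patients").

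Missing data then fixes the order of work: "First, all analyses will be performed without taking into account missing values". Multiple imputation with 10 datasets follows as a sensitivity analysis for the primary and all secondary outcomes. Total planned sample size adds about 5 % for loss on the primary endpoint.

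Definitions says that NIV intolerance "refers to the need for the premature cessation of an NIV session", and Study objectives names NIV tolerance in the primary objective. The data-collection section and Table 1 also schedule a comfort rating at 5 minutes and at the end of every session, and the reason for an early end is recorded. Neither the primary endpoint nor its analysis refers to these items.

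**The concern.** The label and the rule do not fit together. An analysis of all randomized patients cannot also be restricted to those with both ratings. This would matter little if ratings were lost for unrelated reasons. Here, one foreseeable way to have no value after 30 minutes of the session is that the session ended sooner, and the protocol's own definition calls that intolerance. Followed as written, the plan can remove from the primary test some of the patients with the worst response to NIV.

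What is at stake is the between-arm contrast in a small trial. If early stops are more common in the control arm, complete-case analysis understates the benefit of music. If they are more common under music, it overstates it. The same applies to all three pairwise comparisons.

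**Working it through.** **1. The plan's own figures.** Inputs from Sample size calculation and Total planned sample size: difference 2, SD 2.5, power 80 %, two-sided alpha 5 % and then 2.5 %, loss about 5 %. A two-sample t test (noncentral t) gives 26 per arm at 5 % (power 80.7 %) and 31 per arm at 2.5 % (power 80.0 %). Then 31 / 0.95 = 32.6, rounded up to 33 per arm, and 3 × 33 = 99. All stated figures reproduce. The allowance replaces lost numbers (33 × 0.95 = 31.4 per arm). It does nothing about which patients are lost. It also fits a primary analysis that leaves them out.

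**2. Who leaves the primary test.** The outcome is the 30-minute value minus the pre-session value. If the first session stops at, say, 15 minutes and no rating is made at 30 minutes, the change cannot be computed. Under the Missing data rule that patient is not in the t test. No section assigns a substitute value.

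**3. Size of the possible bias.** Let f_c and f_m be the proportions without a 30-minute rating in the control and music arms. Let k be how much worse the mean change of these patients is than that of completers, taken as equal in both arms. Each arm's full mean is its completer mean plus k × f. With benefit defined as control minus music:

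benefit (all randomized) = benefit (complete cases) + k × (f_c − f_m)

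The article gives neither the rates nor k, so all values below are assumptions.

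| Difference in stop rate | k | Bias | Share of the planned 2 |
|---|---|---|---|
| 0 points | any | 0 | 0 % |
| 2 points | 5 | 0.02 × 5 = 0.10 | 5 % |
| 12 points | 5 | 0.12 × 5 = 0.60 | 30 % |
| 5 points (10 % vs 5 %) | 2 | 0.05 × 2 = 0.10 | 5 % |
| 5 points (10 % vs 5 %) | 6 | 0.05 × 6 = 0.30 | 15 % |

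For scale, the standard error of one comparison with 31 per arm is 2.5 × √(2/31) = 0.63.

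**4. What it could do to power, under one assumed mechanism.** Simulated trials: 33 per arm, change normal with SD 2.5, true difference 2, two-sided 2.5 %. Every patient whose change is worse than a common threshold has no 30-minute rating.

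| Lost in control | Lost in music | Mean complete-case difference | Power |
|---|---|---|---|
| 5 % | 0.7 % | 1.79 | 77 % |
| 10 % | 1.9 % | 1.64 | 71 % |
| 15 % | 3.3 % | 1.51 | 64 % |
| 20 % | 5.0 % | 1.40 | 59 % |

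With everyone counted, power is about 83 % (82.7 % by exact calculation). The mechanism is deliberately strict, since it always loses the worst values. It shows only the direction in which the benefit is diluted.

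**The case against.** The strongest reply is that the exclusion is inferred and not stated. Table 1 sets the third time point at session start plus 30 minutes, and nothing says that rating stops when NIV stops. That is right: a centre could read the schedule as requiring the rating regardless. But the endpoint is worded as a value after 30 minutes of the session, so another centre could read it the other way. The text does not settle it.

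Second, the trial collects 5-minute and end-of-session ratings and the reason for stopping, and the imputation draws on observed outcomes. A reader might infer that imputation would treat early stoppers like patients who tolerated NIV. The documents do not support this, since an imputation model could include those ratings, and its detail belongs in an analysis plan that is not shown. What stands is that imputation is only a sensitivity analysis, while the stated primary rule is complete-case.

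Third, intolerance is not lost to the trial. Interrupted sessions, the ratio of observed to prescribed duration, and intubation are compared between arms. That helps interpretation but does not repair the primary test.

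Fourth, the plan expects only about 5 % loss from all causes. If two compared arms average 5 %, the largest possible difference is 10 % against 0 %, or 0.10 × 5 = 0.5 points. The top of the range in the working therefore needs more loss than planned.

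Two stronger readings should be set aside. One is that intolerance of the eye mask ends sessions in the device arms and so flatters music. The sensory-deprivation section offers alternatives to such patients and does not say that NIV stops. The other is that some eligible patients cannot rate themselves, because relatives may be asked about musical taste "if the patient is unable to express her musical choices (moderate impairment of consciousness"). That sentence concerns choosing music. It does not show that a patient cannot mark a ruler.

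**Conclusion.** The point holds in a limited form. As written, the primary analysis is complete-case although it is labelled intention-to-treat of all randomized patients, and the handling of a first session that ends before 30 minutes is not defined. Because such an ending is the protocol's own definition of intolerance, the resulting loss can depend on the outcome. This is a conflict between stated rules and not merely detail left to an analysis plan.

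The size and direction of any bias are unknown. The 0.1 to 0.6 points rest on an assumed 5-point gap, equal in both arms, and an assumed 2 to 12 percentage-point difference in stop rate. With equal rates and gaps the bias is nil. A reader might conclude that the primary result will be wrong by a known amount or in favour of music. Nothing in the article supports either conclusion. The change is worth making because it is cheap, and the sample size need not change.

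**What to change.** - State that the comfort rating is taken 30 minutes after the start of the first session in every randomized patient, whether or not NIV is still running.
- If that rating cannot be obtained, use the end-of-session rating, which is already scheduled, in the primary analysis.
- Keep as sensitivity analyses: complete cases, multiple imputation with the 5-minute and end-of-session ratings in the model, and an analysis giving the worst score to early stops. The worst score is better placed here than in the primary analysis, because in a change score the penalty depends on the baseline (10 − 9 = 1 from a baseline of 9, 10 − 3 = 7 from a baseline of 3).
- Report by arm how many first sessions ended before 30 minutes, and why.

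Settle this before outcomes are compared by arm. For patients already enrolled, the scheduled end-of-session rating can serve.

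The cost is wording and staff instruction. A few ratings will be made off NIV or before 30 minutes, so the endpoint becomes slightly less uniform. A patient with neither rating still has no primary value, and the sensitivity analyses and the counts by arm must cover that case.

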#### Software

The analyses will be performed using R software (R Foundation for Statistical Computing, Vienna, Austria, http://www.R-project.org/) 3.0 or later or SAS version 9.2 or later.

## Safety considerations

In the current study there are no anticipated risks or inconveniences. For this reason, neither safety interim analysis nor stopping rules are planned. Any unexpected medical event after inclusion (adverse events, AEs) will be recorded on the individual CRFs. Unexpected serious adverse events (SAEs) will be reported to the sponsor immediately, and all participating centers will be informed by the sponsor (Department de la Recherche Clinique - Assistance Publique - Hôpitaux de Paris).

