## Background

Acute respiratory failure (ARF) is the most frequent organ failure in patients in the intensive care unit (ICU) [1]. Among the various respiratory supports, non-invasive ventilation (NIV) allows the administration of a positive pressure of air and oxygen, at a set inspiratory flow and FiO_2_, which unloads respiratory muscles and enables alveolar recruitment. NIV has shown its efficacy in acute or chronic respiratory failure [2] and cardiac pulmonary edema [3] in terms of intubation rates [4, 5], mortality [5], and nosocomial infections [6]. These positive findings have not been so clearly found in de novo ARF, where NIV benefits may be outweighed by the risks of delaying intubation [7, 8], which has been associated with increased mortality [8]. Although NIV offers many undisputable advantages over invasive ventilation, its intolerance is one of its major drawbacks. Also, premature cessation of NIV because of intolerance may lead to intubation in some cases [7–9]. Hence, investigators have searched for means of improving tolerance of the technique by increasing patient comfort. Light sedation has been shown to decrease NIV-induced discomfort [10–13] and appears to be safe and effective, but this alternative remains a pharmacologic intervention requiring the administration of potentially dangerous anesthetic drugs, such as propofol, remifentanil, or dexmedetomidine. Among non-pharmacologic interventions, sophrology, which aims at increasing well-being through differential relaxation, has been assessed with interesting results [14]. However, only a limited number of patients have been evaluated, and the major drawback is the need for patient adherence, a specific caregiver’s training, and the presence of a single person with the patient for an entire 30-minute session, which makes it very dependent on the availability of the team.

Music therapy in health care settings has recently been investigated. In the perioperative setting, it has shown beneficial effects on anxiety, pain, analgesia use, and patient satisfaction [15]. In the ICU, several studies [16–19] and a recent meta-analysis [20] described its effects in terms of anxiety and physiological changes (heart rate, respiratory rate, and blood pressure) in patients on invasive mechanical ventilation. These studies showed that music therapy is feasible in the ICU, with beneficial effects on physiological parameters, anxiety, and agitation.

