#### “Sensory deprivation” group

In this group, NIV is conducted similarly as for the former group but with the addition of sensory deprivation. Sensory deprivation consists of isolating participants from the noise and lights of the ICU:An insulating around-ear headphone (BOSE AE2®, the same as that used in the latter intervention arm) is placed on the patients’ ears by the unblinded caregivers, once the NIV mask has been fitted and the ventilator settings optimized.Applying a sleeping mask conceals the eyes. If the patient does not tolerate being blindfolded (e.g., due to claustrophobia), alternative solutions are suggested to the patient (such as closing his eyes or using a personal scarf) to make him feel at ease. The purpose of the visual deprivation is to avoid the patient being disrupted from the relaxation process because of visual distractions.

The headphones and mask will be left in place for 30 minutes. Data regarding tolerance and possible rejection of sensory deprivation will be collected.

After inclusion, all NIV sessions are conducted as detailed above until NIV discontinuation, day 28, or ICU discharge.

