##### Percentage of patients requiring physical restraints or administration of anxiolytics or sedatives during NIV sessions, percentage of intubated patients

These percentages will be compared between groups by the usual tests for comparing proportions.

##### SF-36, HADS scores, IES-R scores, and overall assessment of NIV between inclusion and day 90

The evolution of these scores between baseline and day 90 (difference between the measurement at 3 months and inclusion) will be compared between groups by the usual tests comparing continuous variables.

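### The safety section anticipates no risk or inconvenience and limits adverse event recording to unexpected events, which conflicts with the protocol's own text; intubation timing and mortality by arm are not among the stated comparisons

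*Protocol article*

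**What the plan says.** The Safety considerations section opens with "In the current study there are no anticipated risks or inconveniences". It makes that the reason for its approach: "For this reason, neither safety interim analysis nor stopping rules are planned". Two recording rules follow: "Any unexpected medical event after inclusion (adverse events, AEs) will be recorded on the individual CRFs", and "Unexpected serious adverse events (SAEs) will be reported to the sponsor immediately".

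Other sections of the article bear on this:

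- **Background**, on NIV in de novo acute respiratory failure: "where NIV benefits may be outweighed by the risks of delaying intubation [7, 8], which has been associated with increased mortality".
- **Sensory deprivation group**: "If the patient does not tolerate being blindfolded (e.g., due to claustrophobia), alternative solutions are suggested to the patient". Data on tolerance and rejection of the isolation are to be collected.
- **Study objectives**: the hypothesis is that the musical intervention improves NIV tolerance.
- **Study population** and **Inclusion and exclusion criteria**: adults with acute respiratory failure for whom the physician considers NIV indicated. De novo failure is not excluded.
- **Secondary endpoints**: intubation is a percentage of patients. The analysis section on restraints, sedatives and intubation says: "These percentages will be compared between groups by the usual tests for comparing proportions".
- **Data collection and follow-up**, with Table 1: need for intubation, exact session duration and reason for premature ending at each session; NIV complications; nasal bridge lesions; vital status at ICU discharge and then to the end of the study.

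Mortality is not in the list of secondary endpoints, and the article describes no comparison of it between arms.

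**The concern.** Expectedness normally decides which serious events go to the sponsor urgently. Here it also decides what is written down at all. In ICU patients with acute respiratory failure, many serious events, including respiratory deterioration, can fairly be called expected. A randomized trial reveals an excess of such events only if they are recorded in every arm, expected or not.

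The premise matters because the interventions are meant to help patients tolerate NIV. If they succeed, they may change how long patients stay on it. The Background says that in part of this population a longer stay can be harmful, through late intubation. The planned intubation endpoint counts how many patients are intubated, not when. At stake is whether a conclusion that the interventions are harmless would rest on data arranged to test it.

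**Working it through.** **1. The statement against the rest of the text.**

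- *Inconvenience.* None is anticipated under Safety considerations, yet the Sensory deprivation group section foresees intolerance of the blindfold, gives claustrophobia as an example and prepares alternatives. This is a direct conflict and concerns the intervention itself.
- *Risk.* None is anticipated, yet the Background names delayed intubation with increased mortality. This is a tension rather than a direct conflict: the Background attributes the risk to NIV, which all three arms receive. The link to music or isolation is an inference from the aim of better tolerance.

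**2. What is captured without the adverse event rule.**

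| Harm | Captured elsewhere? | Compared by arm? |
|---|---|---|
| Need for intubation | Yes, each session | Yes, as a percentage |
| Time to intubation | Not listed; session data allow an approximation | Not stated |
| Death | Yes, vital status to day 90 | Not stated |
| NIV complications, nasal bridge lesions | Yes | Not stated |
| Rejection of isolation, pulling at mask or headphones | Yes | Not stated |
| Respiratory rate, saturation, tidal volume, heart rate, arterial pressure | Yes, repeatedly in each session | Yes, mixed model |
| Other serious events that count as expected | Not required | No |

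The last row is the gap that the word *unexpected* creates. The second and third rows are gaps in the stated comparisons.

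**3. Why a percentage misses timing.** With x of n patients intubated in an arm, the endpoint is x/n. If the same x patients are intubated later, within the same observation period, x and n do not change and the difference between arms does not move, whatever the length of the delay.

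**4. What 33 per arm can show.** The safety section gives no figure of its own, so the arm size comes from the sample size section, and it reproduces. Inputs: difference 2, SD 2.5, power 80 %, two-sided. The *t* test calculation gives 25.5, rounded up to 26 per arm, at 5 %, and 30.99, rounded up to 31, at 2.5 %. Allowing for 5 % loss, 31/0.95 = 32.6, rounded up to 33; 3 × 33 = 99.

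The documents give no intubation or death rate, so control rates of 10 to 40 % are assumed. For two proportions with n = 33 per arm at two-sided 5 %:

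power = Φ{ [ |p₂ − p₁| − 1.96 √(2p̄(1 − p̄)/n) ] / √[ (p₁(1 − p₁) + p₂(1 − p₂))/n ] }, where p̄ is the mean of p₁ and p₂.

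Example, 20 % against 30 %: p̄ = 0.25; first root √(2 × 0.1875/33) = 0.1066; second root √((0.16 + 0.21)/33) = 0.1059; (0.10 − 1.96 × 0.1066)/0.1059 = −1.03; Φ(−1.03) = 0.15.

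| Assumed control rate | Power, 1.5-fold rise | Power, doubling | Rate detectable with 80 % power |
|---|---|---|---|
| 10 % | 9 % (to 15 %) | 20 % (to 20 %) | about 39 % |
| 20 % | 15 % (to 30 %) | 42 % (to 40 %) | about 53 % |
| 30 % | 24 % (to 45 %) | 70 % (to 60 %) | about 64 % |
| 40 % | 37 % (to 60 %) | 93 % (to 80 %) | about 74 % |

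A non-significant comparison of intubation or death would therefore say little about safety.

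**The case against.** The strongest reply is that intubation and death do not depend on the adverse event wording at all. Both are collected for every patient, and intubation is compared by arm. Physiological deterioration in a comfortable patient would be looked for in the repeated respiratory and hemodynamic measurements, which are modelled by arm. This stands. A reader might infer from the safety section that the trial could not see the harm its Background names, or that every planned outcome would come out neutral or favourable. The documents do not support either reading.

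Second, the statement can be read as referring only to the added interventions. The treating physician decides that NIV is indicated and prescribes the sessions, patients are monitored for complications, and each unit applies its own intubation criteria. The music or isolation is planned for 30 minutes per session, with an extension of the music on request. This also stands in part: nothing in the article shows that the interventions prolong failing NIV, or by how much. The Discussion's cited figure of 14 % of NIV failures from intolerance does not help. That the remaining 86 % (100 − 14) would only be postponed does not follow. The reading does not, however, remove the conflict with the foreseen blindfold intolerance, which belongs to the intervention.

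Third, the article condenses a longer protocol. Full adverse event definitions, a mortality table or a time-to-intubation analysis may sit in that protocol or in the analysis plan, and *unexpected* may be a loose word for untoward. The absence of such analyses alone would therefore not be a finding. But the recording rule is stated, not omitted, and it uses the same qualifier for serious events, where the word has a specific meaning. As written, it restricts recording.

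**Conclusion.** The point holds in a limited form. The claim that no risk or inconvenience is anticipated conflicts with the foreseen blindfold intolerance and sits badly with the Background's warning on delayed intubation. The stated rule lets expected serious events go unrecorded unless a dedicated field catches them. The intubation endpoint does not reflect timing, and no mortality comparison by arm is stated, although vital status is collected.

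The primary analysis is unaffected and the sample size reproduces. The consequence is for what the trial may say about safety: with 33 per arm, power for a 1.5-fold rise in intubation or death is 9 to 37 %, under assumed control rates of 10 to 40 %. Two things rest on inference or assumption: that the interventions could delay intubation, and the event rates. The conflict in the text and the wording of the recording rule rest on neither.

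**What to change.** 1. Reconcile the Safety considerations section with the Background and the Sensory deprivation group section, so that the foreseen inconvenience and the named risk of NIV are acknowledged.
2. Record all serious adverse events after randomization, expected or not, and tabulate them by arm. Keep immediate reporting to the sponsor for the unexpected ones.
3. Report, as descriptive safety outcomes by arm, the time from the first randomized NIV session to intubation, and mortality from the vital status already collected. If the case report form has no intubation date and time, add that field.
4. State that 33 per arm gives low power for harm, so the absence of a significant difference is not to be read as evidence of safety.

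The cost is some additional serious adverse event entries, one date/time field for about 99 patients and a few tables. The sample size and the primary analysis stay as they are, and none of these changes requires an interim analysis or an extra committee.
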